**5.5. How often will a report, regarding the outcome of the review by the DSMB/DSMC, be sent to the UVa PI?**

A copy of these reports must be sent to the IRB if applicable as soon as they are received by the PI. Do not wait until the next continuation to submit them to the IRB.

__X___NA- PI is not the overall person overseeing the safety data for this study.

**5.6. How will a report of the information discussed in question 5.4 OR 5.5 be submitted to the IRB?**

__X___Part of IRB-HSR continuation status form

# Payment

**1. Are subjects being reimbursed for travel expenses** (receipts /mileage required)**?** NO

**2. Are subjects compensated for being in this study?** YES

►IF YES, answer the following questions (2a-2d).

**2a. What is the maximum TOTAL compensation to be given over the duration of the protocol?** $150 if non-bariatric subject and $500 if a bariatric patient

**2b. Explain compensation to be given.**

Bariatric subjects will be compensated per completion of phases:

Completion of Phase 1-3: $**100 (or $150 if pre-test fat biopsy performed)**

Completion of Phase 4-5: $**250**

Completion of Phase 7: $**100**

***Total payment***: **$450 (or $500 if fat biopsy performed in phase 3)**

Non-Bariatric subjects will be compensated per completion of phases:

Completion of Phase 1-3: $**50 (or $75 if pre-test fat biopsy performed)**

Completion of Phase 4-5: $**50 (or $75 if post-test biopsy performed)**

***Total payment***: **$100 (or $150 if fat biopsies performed)**

Please note for **Bariatric Surgery**

Subjects are having bariatric surgery and related tests as part of their clinical care. Subjects and/or their insurance company must pay for any tests or care required for your clinical care. In addition, subjects and/or their insurance company may also have to pay for other drugs and treatments that are given to help them control any side effects. Subjects will have to pay for any costs not covered by their health plan. Subjects may be responsible for any co-payments or deductibles.

**2c. Is payment pro-rated?** YES

**2d. Is money paid from UVa or State funds (including grant funds) or will items such as gift cards be distributed through UVa?**

Yes, the Curry School Foundation and School of Medicine

►IF YES, answer the following questions [2d(i)-2d(ii)].

**2d(i). How will the researcher compensate the subjects?**

__X___ Check issued to participant via UVA Oracle or State system

**2d(ii). Which category/ categories best describes the process of compensation?**

Choose one of the following 3 options

__X___ All compensation will be made via check issued to participant via UVA Oracle or State system

The preferred method

# Risk/ Benefit Analysis

1. What are the potential benefits for the participant as well as benefits which may accrue to society in general, as a result of this study?

Upon completion of the study participants will receive a report detailing their individual results (e.g. body composition, fitness, effects of exercise on post prandial hyperglycemia). Society in general will benefit from greater understanding of the importance of exercise and/or diet in insulin resistance and maintaining healthy immune cell profiles in individuals undergoing bariatric surgery who are at high risk for developing Type 2 diabetes and CVD.

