# Brief Summary/Abstract

Obesity is a major health concern that has been associated with an estimated 2.8 million deaths worldwide each year. The number of individuals considered obese with a Body Mass Index (BMI) above 30 kg/m^2^ has grown to more than 500 million. The increased morbidity and mortality associated with obesity stems from a long list of comorbidities, including hypertension, coronary artery disease, stroke, cancer, and type 2 diabetes (T2D). Bariatric surgery is an emerging intervention that has been used frequently to induce weight loss for obese individuals and it has been shown to improve glycemic control and insulin resistance in people at risk for type 2 diabetes. Beyond weight loss and improved glycemic control, surgery may lead to healthy improvements in inflammation, immune cells and vascular health. It is already known that exercise and weight loss from lifestyle modification can improve glycemic control, insulin resistance, levels of inflammatory cytokines, gut bacteria and arterial stiffness. However, no work has been done to examine a combination of bariatric surgery and pre-surgery lifestyle modification with diet and exercise. Recent work by our team has evidence demonstrating that health status pre-surgery has an impact on post-surgery outcomes. Such findings suggest that improvements in health status from exercise and/or caloric restriction before surgery may improve surgery outcomes as well as surgery-induced health outcomes. To date, no study has systematically examined the role of diet and/or exercise on the prevalence of surgery complications or on post-surgery weight loss, glycemic control, and insulin resistance. Moreover, no work currently exists with lifestyle modification, with or without bariatric surgery on adipose tissue derived inflammation related to immune cells or gut bacteria. Therefore, the purpose of this study is to investigate the effect of pre-surgery lifestyle intervention with diet and/or exercise on bariatric surgery outcomes. To test this objective, subjects will participate in a match paired study, based on BMI. Subjects will undergo testing of blood chemistry and related measures of health before and after lifestyle intervention, as well as 4 weeks post-bariatric surgery. The subjects will be match paired to standard care or exercise until these interventions are filled. Once standard care and exercise interventions are full subjects will then be match paired to exercise plus diet and then diet last. After the intervention all subjects will receive surgery. Post surgery outcomes will be assessed by examining surgery operating time, changes in blood chemistry, adipose tissue biopsies and other measures indicative of glucose and vascular health.

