**►IF YES, explain the kind of controls to be used.**

Subjects will have pre-intervention testing to determine efficacy of exercise and/or diet on insulin sensitivity and immune health.

1. **What is the study design?**

Matched pair, prospective design. Bariatric patients will be match paired to the exercise or standard medical care group. Subjects not undergoing bariatric surgery will be randomized to calorie restriction or calorie restriction + exercise groups.

1. **Does the study involve a placebo?**

No

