***Phase 4: Interventions***

Prior to the intervention subject’s undergoing bariatric surgery will be match paired to receive either standard medical care (SC) or exercise + standard care for 4 weeks. Subject’s not undergoing bariatric surgery will then be randomized to the exercise + diet + standard care group or diet + standard care group for 2 weeks.

*Standard medical care:* If subjects are assigned to this group they will not be provided materials to consume healthy diet and increase exercise participation. Subjects will also be asked to participate in the standard education sessions that are provided to all bariatric surgery patients. This standard care includes meetings with a nutritionist, a psychologist, and a bariatric surgeon.

*Diet + standard medical care*: If subject’s are assigned to this group they will be instructed to follow a weight loss diet plan, created for them by the research team. The diet will restrict your caloric intake to 1000-1400 calories per day. Subject’s will be given two meal replacement shakes each day and advice for preparing a standard, calorie-limited dinner designed for weight loss. Subjects are required to pick up food at least 1 time a week. Subjects will return empty bottles of meal shakes to confirm compliance.

*Exercise training* + *standard medical care for bariatric patients*: If subject’s are assigned to this group they will participate in exercise training and the standard medical care outlined above. Subject’s will be asked to exercise 5 days/week. Subject’s will be able to attend regularly supervised and scheduled training sessions with the exercise physiology staff members in Memorial Gym or they can exercise on their own. Overall, the training program will ask subject’s to exercise 5 times per week and 30 min/day. Subject’s heart rate will be monitored continuously during all training sessions, and they will be asked to exercise at an intensity 65-85% of their previously measured HRmax. Walking will be the main type of exercise. In addition to this training program, subject’s will participate in the standard education sessions that are provided to all bariatric surgery patients.

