**Study Schedule Visit Overview for Non-Bariatric Subjects**

| **Study Visit** | **Screening Visit 1** | **Screening Visit 2^** | **Pre-Test Visit 3** | **Exercise Training**  **Visits 4-17** | **Diet Pick Up****  **Visits**  **4-5** | **Post-Intervention Testing**  **Visit 18**  **(or Visit 6)** |
| --- | --- | --- | --- | --- | --- | --- |
| Consent | X |  |  |  |  |  |
| Blood Draw | X |  | X |  |  | X |
| History and Physical |  | X | X |  |  | X |
| Urine Collection (Nitrogen & Microparticle Analysis) |  |  | X |  |  | X |
| Stool Collection  (Gut Bacteria) |  |  | X |  |  | X |
| VO2peak (Cycle ergometer testing) |  | X |  |  |  | X |
| Timed Walk Test (6-MWT) |  | X |  |  |  | X |
| Body Fat measurement |  | X |  |  |  | X |
| Adipose Biopsy |  |  | X |  |  | X |
| OGTT |  |  | X |  |  | X |
| Indirect Calorimetry |  |  | X |  |  | X |
| Blood Pressure, FMD, AI, and PWV tests |  |  | X |  |  | X |
| Diet Record |  |  | X |  |  | X |
| Appetite Questions |  |  | X |  |  | X |
| Quality of Life Questions |  |  | X |  |  | X |
| Laval Questionnaire |  |  | x |  |  | x |
| Accelerometer |  | X |  |  |  | X |
| Heart Rate Monitors |  |  |  | X |  |  |
| Meal Shakes |  |  |  |  | X |  |
| Urine Pregnancy Test (women) |  | X | X |  |  | X |

Note: Subjects will be randomized to diet or diet+exercise intervention group. ^Visit 2 is designed to be performed in 1 day. However, if time does not permit this day may be separated in to 2 visits to accommodate needs. Also, we perform fitness and body fat tests within 3 days post blood work to minimize any time constraint involved in blood work tests. ** Exercise Training for subjects not receiving bariatric surgery will be performed at UVA in Memorial Gymnasium and fully supervised by an exercise physiologist. *** Meal Shakes will be provided for the diet. Subjects are asked to pick up these meal shakes 1 time a week and return empty bottles. If subjects are also exercising, diet shakes will be picked up during training sessions.

**3. Will you be using data/specimens in this study that were collected previously, with the use of a research consent form, from another research study?** NO

**4. Will any of the procedures listed in item # 2 have the potential to identify an incidental finding? This includes ALL procedures, assessments and evaluations that are being done for RESEARCH PURPOSES that may or may not be considered investigational.**

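### The study diet is given only to non-surgical subjects, so the trial cannot support the stated purpose and benefit concerning diet in people undergoing bariatric surgery

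*Protocol*

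**What the plan says.** Abbreviations: SC, standard care; Ex, exercise plus standard care; CR, calorie restriction; Ex+CR, both.

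- **Claims.** The Brief Summary/Abstract says "the purpose of this study is to investigate the effect of pre-surgery lifestyle intervention with diet and/or exercise on bariatric surgery outcomes". It describes four matched groups, the two diet groups filling last, and adds "After the intervention all subjects will receive surgery". Risk/ Benefit Analysis, item 1, refers to greater understanding of the "importance of exercise and/or diet in insulin resistance and maintaining healthy immune cell profiles in individuals undergoing bariatric surgery".
- **Allocation.** Study Design says "Bariatric patients will be match paired to the exercise or standard medical care group" and "Subjects not undergoing bariatric surgery will be randomized to calorie restriction or calorie restriction + exercise groups". Phase 4 repeats this: surgical subjects are "match paired to receive either standard medical care (SC) or exercise + standard care for 4 weeks", and the others are "randomized to the exercise + diet + standard care group or diet + standard care group for 2 weeks".
- **Schedules.** The note to the non-bariatric schedule says "Subjects will be randomized to diet or diet+exercise intervention group". Meal shakes and diet pick-up appear only in that schedule. The surgery and post-surgery visits appear only in the bariatric one.
- **Objectives (Hypothesis to be Tested).** Objectives 1 and 2 name Ex+CR vs CR and Ex vs SC. Objective 2 applies both to surgical complications. Objective 3 lists all four groups, for a correlation of circulating with adipose immune measures.
- **Analysis (Statistical Considerations).** Four conditions are analysed by a group-by-test repeated measures ANOVA, with Bonferroni group comparisons and paired t-tests within arms.

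**The concern.** To learn what diet does, the trial needs subjects with and without the diet who are otherwise comparable. Here every subject on the diet is non-surgical and every subject off it is surgical. Both planned within-cohort contrasts isolate exercise. The remaining contrasts, CR vs SC and Ex+CR vs Ex, compare two populations treated for different lengths of time and tested with different challenges.

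A reader who relies on the stated purpose could take such a cohort difference for an effect of pre-operative diet. The benefit statement, which forms part of the risk/benefit justification, would then rest on no surgical patient who had been given the study diet.

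**Working it through.** **1. Arms**, from Study Design, Phase 4, Blood draws and the two visit schedules:

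| Arm | Cohort | Study diet (D) | Study exercise (E) | Non-surgical (C) | Duration | Test |
|---|---|---|---|---|---|---|
| SC | surgical | 0 | 0 | 0 | 4 weeks | MMTT |
| Ex | surgical | 0 | 1 | 0 | 4 weeks | MMTT |
| CR | non-surgical | 1 | 0 | 1 | 2 weeks | OGTT |
| Ex+CR | non-surgical | 1 | 1 | 1 | 2 weeks | OGTT |

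Human Participants gives 16 treated surgical and 28 treated non-surgical subjects, so the diet reaches 0 of 16 and 28 of 28. (That section's summary line says 50 treated, whereas 16 + 28 = 44. The argument needs only the proportions 0 and 1.)

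**2. Estimability.** Write the arm mean as μ + εE + δD + κC, where κ holds everything that goes with cohort. Then:

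- SC = μ; Ex = μ + ε; CR = μ + δ + κ; Ex+CR = μ + ε + δ + κ
- Ex − SC = ε, and Ex+CR − CR = ε
- CR − SC = δ + κ, and Ex+CR − Ex = δ + κ

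Columns D and C are identical, so the matrix (intercept, E, D, C) has rank 3 of 4. Exercise is estimable. Diet and cohort are estimable only as their sum. Adding E×D and E×C gives rank 4 of 6, so that interaction is aliased too. Adding pre/post time and its interactions to the four-column model gives rank 6 of 8: exercise × time is estimable and diet × time is not. Using change from baseline therefore does not help. Besides population, κ contains duration, metabolic test, ergometer and exercise programme.

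**3. The one sizing figure built on a diet contrast.** The sample-size section takes exercise 3.7 kg against exercise+diet 6.8 kg, SD 3.1 kg, and reports 10 subjects. The standardised difference is (6.8 − 3.7)/3.1 = 1.0. At 80% power and alpha 0.05, with two sides assumed because none are stated, a one-sample or paired t-test needs 9.94, that is 10, so the figure reproduces in that form. A two-group t-test needs 16.7, that is 17 per group.

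For the present point, what matters is which contrast was used. Exercise versus exercise+diet differs in diet. In this trial that pair is Ex (surgical) and Ex+CR (non-surgical), which crosses cohorts. The groups being sized are CR and Ex+CR, which differ in exercise.

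**4. Surgical outcomes.** Operating time, complications and post-operative tests come from Phases 6 and 7, both marked as applying only where relevant, and from visits found only in the bariatric schedule. Subjects with both the study diet and a surgical outcome: 0. Objective 2's Ex+CR vs CR comparison of complications therefore has no data in either arm.

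**5. The abstract's scheme.** If all four groups were surgical, as the abstract has it, diet would not be aliased with cohort. But the diet groups would open only after SC and Ex were full, so diet would be aliased with enrolment period instead, still without a concurrent no-diet comparator.

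**The case against.** - **The benefit statement is soft.** It speaks of greater understanding, in a form answer on benefit to society. A reader might infer that the protocol promises to show the importance of diet in surgical patients; the text does not go that far. The abstract's statement of purpose is less easily excused, since it names diet and surgery outcomes directly.
- **The operative sections are more modest.** Hypothesis to be Tested speaks of separate studies, expects Ex+CR to beat CR and Ex to beat SC, and says the work will shape later studies in bariatric patients. That stands, and it supports narrowing the claims. It does not clear the section: objective 2 asks for surgical complications in non-surgical arms, and objective 3 lists all four groups together.
- **Some diet information exists.** A reader might infer that nothing about diet can be estimated. That is too strong: the planned paired t-tests give a pre/post change in the CR arm. It is uncontrolled and comes from non-surgical subjects only.
- **The abstract may simply describe another design.** True, and that contradiction needs resolving in its own right. Step 5 shows that adopting it would not rescue a diet effect.
- **No factorial model is planned.** Correct: the protocol analyses by group. The rank calculation only shows what any group comparison can identify. Nor does the protocol say that CR vs SC or Ex+CR vs Ex will be read as diet effects; it leaves that reading open.
- **Surgical patients do see a nutritionist.** They do, as part of standard care, but both surgical arms have this, so it creates no diet contrast.

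**Conclusion.** The point holds for the design in Study Design, Phase 4 and the two schedules. No controlled diet effect is identified, whatever the sample size, and an analysis plan could not restore one, because the allocation itself creates the aliasing. No effect of diet on surgery outcomes can be estimated. The purpose in the abstract, the benefit statement and objective 2 therefore extend beyond what the trial can deliver.

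The conclusion assumes that the detailed sections, rather than the abstract, govern allocation, and that cohort differences are not simply taken to be zero; the documents give no basis for taking them so. It does not call into question Ex vs SC or Ex+CR vs CR as contrasts within their own cohorts. The change is one of stated scope and should be made, but it affects no measurement or procedure.

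**What to change.** 1. Reconcile the abstract's four matched groups and its statement about surgery for everyone with Study Design, Phase 4, Phase 6 and the non-bariatric schedule.
2. If the detailed design stands, restate the abstract's purpose, objective 2 and Risk/ Benefit item 1. The trial estimates (a) exercise added to standard care in surgical candidates and (b) exercise added to calorie restriction in obese subjects not having surgery. Limit surgical outcomes to Ex vs SC and remove diet from statements about bariatric patients.
3. In Statistical Considerations, and at objective 3, state that comparisons across cohorts (CR vs SC, Ex+CR vs Ex) will not be interpreted as diet effects, and that pre/post change in the CR arm is descriptive and uncontrolled.
4. In the sample-size section, state that the exercise versus exercise+diet difference does not correspond to a within-cohort contrast of this trial.

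Cost: protocol wording and a narrower stated scope. No extra subjects or procedures are needed.

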**2. Do the anticipated benefits justify asking subjects to undertake the risks?**

Yes, since the health benefits of exercise clearly outweigh the risk involved, particularly in morbid obese subjects who are at an elevated risk of future disease. While the current study is examining the short-term exercise effects, participants may be more empowered to incorporate exercise into their daily lives after successful completion of the testing sessions as well as from greater understanding of the importance of exercise on glucose control and vascular health.

# APPENDIX: Legal/Regulatory

**Recruitment**

The following procedures will be followed:

- Finders fees will not be paid to an individual as they are not allowed by UVa Policy.
- All recruitment materials will be approved by the IRB-HSR prior to use. They will be submitted to the IRB after the IRB-HSR has assigned an IRB-HSR # to the protocol.
- Only those individuals listed as personnel on this protocol will recruit and or conduct the consenting process with potential subjects.

**Retention Incentives**

Any item used by the sponsor/ study team to provide incentive to a subject to remain in the study, other than compensation identified in the Payment section, will be submitted to the IRB for review prior to use. The IRB-HSR will provide the study team with a Receipt Acknowledgement for their records. Retention incentive items are such things as water bottles, small tote bags, birthday cards etc. Cash and gift cards are not allowed as retention incentives.

**Clinical Privileges**

The following procedures will be followed:

- Investigators who are members of the clinical staff at the University of Virginia Medical Center must have the appropriate credentials and been granted clinical privileges to perform specific clinical procedures whether those procedures are experimental or standard.
- The IRB cannot grant clinical privileges.
- Performing procedures which are outside the scope of the clinical privileges that have been granted may result in denial of insurance coverage should claims of negligence or malpractice arise.
- Personnel on this protocol will have the appropriate credentials and clinical privileges in place before performing any procedures required by this protocol.
- Contact the Clinical Staff Office- [name] or [name] for further information.

**Sharing of Data/Specimens**

Data and specimens collected under an IRB approved protocol are the property of the University of Virginia. You must have “permission” to share data/ specimens outside of UVa other than for a grant application and or publication. This “permission” may come in the form of a contract with the sponsor or a material transfer agreement (MTA) with others. A contract/ MTA is needed to share the data outside of UVa even if the data includes no HIPAA identifiers and no code that could link the data back to a HIPAA identifier.

- No data will be shared outside of UVa, beyond using data for a grant application and or publication, without a signed contract/MTA approved by the SOM Grants and Contracts office/ OSP or written confirmation that one is not needed.
- No specimens will be shared outside of UVa without a signed contract/MTA approved by the SOM Grants and Contracts office/ OSP or written confirmation that one is not needed.

**Prisoners**

If the original protocol/ IRB application stated that no prisoners would be enrolled in this study and subsequently a subject becomes a prisoner, the study team must notify the IRB immediately. The study team and IRB will need to determine if the subject will remain in the study. If the subject will remain in the study, the protocol will have to be re-reviewed with the input of a prisoner advocate. The prisoner advocate will also have to be involved in the review of future continuations, modifications or any other reporting such as protocol violations or adverse events.

Prisoner- Individuals are prisoners if they are in any kind of penal institution, such as a prison, jail, or juvenile offender facility, and their ability to leave the institution is restricted. Prisoners may be convicted felons, or may be untried persons who are detained pending judicial action, for example, arraignment or trial.
For additional information see the OHRP website at <http://www.hhs.gov/ohrp/policy/populations/index.html>

